### Data collection

All study participants must weigh themselves once at the start of the study and at 1, 6, 12, and 24 months postpartum and track their activity and sleep patterns for 1 week at the beginning of the study and at 6, 12, and 24 months postpartum. Body weight will be measured once a day in the morning using the weight and body composition monitor. Activity and sleep will be measured using an activity and sleep tracker, which will be worn on the non-dominant arm at all times, even during sleep, except during recharging (once every 5 days).

All participants will complete online questionnaires at the beginning of the study and at 1, 6, and 12 months postpartum. If any data are lacking, they will be collected from the medical records. Details of the questionnaires developed for this study are as follows (supplementary file):

Background and lifestyle (at the start of the study): items related to pregnancy and delivery history, medical history, family history, and exercise and dietary habits.Edinburgh Postnatal Depression Score (EPDS) (start of study, 1 month postpartum) [22].Breastfeeding status (intensity, duration) questionnaire (1, 6, 12 months postpartum).Breastfeeding process questionnaire (1 month postpartum).Behavioral changes (attitude, knowledge) (6, 12 months postpartum).User-friendliness of devices, barriers to lifestyle improvements and behavioral changes, areas for improvement, etc. (6, 12 months postpartum) (both groups).Desire to continue using the IoT devices after the trial ends (12 months postpartum) (intervention group only).

All participants will have blood samples taken at home via postal self-checkups at 6, 12, and 24 months postpartum to measure HbA1c, fasting glucose, total protein, albumin, AST, ALT, γ-GTP, total cholesterol, HDL cholesterol, triglycerides, urea nitrogen, creatinine, and uric acid. To collect blood samples, the trial secretariat will send test kits to the participants for postal self-checkups. Results of the postal self-checkups will be returned by mail to the participants within 6 weeks.

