All participants will measure their blood pressure at home over 3 days at 6, 12, and 24 months postpartum. The HBF-227t sphygmomanometer manufactured by OMRON Healthcare Co. will be used. Measurements will be taken twice a day in the morning (within 1 h of waking up, after urinating, before taking any medication, and after resting for 1–2 min) and before going to sleep (after resting in the sitting position for 1–2 min). In principle, two measurements will be taken each time.

Table 1 shows the schedule for the trial.

**Table 1 Tab1:** Study timeline for intervention and data collection

		Trial duration								
		Obtain consent		Intervention						Completion
Pregnancy, postpartum			Start of trial	During pregnancy	Delivery	1 month postpartum	6 weeks postpartum	6 months postpartum	12 months postpartum	24 months postpartum
	Obtain consent	×								
	Registration	×								
Regular management	Regular medical care, guidance (maternity checkups)Regular health guidance			○ (maternity checkup→→		○ (1-month postpartum checkup)				
Measure at home	Weight, body composition		○			○		○	○	○
	Activity, sleep		○					○	○	○
Blood pressure	Blood Pressure							○	○	○
Postal checkups	Postal checkup (blood glucose, HbA1c, etc.)							○	○	○
App intervention	Weight, activity, sleep		●	→→→→→→→			●→→→	→→→→→→	→	
	Meal photos		●	→→→→→→→			●→→→	→→→→→→	→	
Mother and Child Handbook	Maternity checkup data (urine test, blood pressure, weight)					○				
	Pregnancy outcome data					○				
Questionnaire	Background, lifestyle		○							
	EPDS		○			○				
	Breastfeeding status					○		○	○	
	Breastfeeding process					○				
	Behavioral changes (attitude, knowledge)		○					○	○	
	User-friendliness of devices							○	○	
	Desire to continue using IoT after end of study								●	

○ Both groups, ● intervention group only

If there are missing data, the research coordinator at each site and trial secretariat will contact the participants. Data from the weight and body composition monitor, activity and sleep tracker, and online questionnaires will be stored on the Internet server. The data file will be secured with a password, and access to information will be limited to designated members such as the researchers and the trial secretariat. Paper-based documents such as consent forms will be stored at each site.

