### Secondary outcomes

The following items will be evaluated (shown in Table 2):

**Table 2 Tab2:** Primary and secondary outcomes

Outcomes				Trial duration							
					Intervention						Finished
				Registration	During pregnancy	Delivery	1 montha postpartum	6 weeks postpartum	6 months postpartum	12 months postpartum	24 months postpartum
Primary			Rate of change in body weight from before pregnancy to 12 months postpartum	×						×	
Secondary	Health outcomes	Bothgroup	Pregnancy outcomes (cesarean section rate, preterm birth rate, LGA rate, excessively large baby rate, pregnancy-induced hypertension rate, gestational diabetes rate, etc.)			×					
			Rate of change in body weight from before pregnancy	×			×		×		×
			Percentage who reached the weight target						×	×	×
			Body fat ratio				×		×	×	×
			Hypertension rate						×	×	×
			Impaired glucose tolerance rate						×	×	×
			Edinburgh Postnatal Depression Score ≥9 rate	×			×				
	Behavioral changes		Number of steps	×					×	×	×
			Sleep	×					×	×	×
			Attitude, knowledge	×					×	×	
			Breastfeeding rate				×		×	×	
			Breastfeeding process				×				
		Intervention group only	Percentage of carbohydrates, fat, protein, dietary fiber in diet	×					×	×	
	Use of IoT/mobile app		Rate of use of weight-body composition monitor, activity-sleep tracker	×					×	×	
			Number of logins to mobile app, browsing time	×					×	×	
			Meal image/content upload status	×					×	×	
			Intervention program continuation rate						×	×	
			Adherence	×					×	×	×
			Desire to continue using IoT after end of study	×						×	
		Bothgroup	User-friendliness of the devices	×					×	×	

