#### Behavioral changes

✓ Attitude, knowledge(Based on relevant questionnaire items).✓ Mean total caloric intake (kcal/day), percentage of carbohydrates in total caloric intake (%)✓ Mean carbohydrate intake (g/day)✓ Percentage of fat in total caloric intake (%)✓ Mean fat intake (g/day)✓ Percentage of protein in total caloric intake (%)✓ Mean protein intake (g/day)✓ Mean dietary fiber intake (g/day)✓ Mean salt intake (g/day)For the intervention group only, the above will be calculated from the data entered into the mobile application (Calo Mama Plus Ninsanpu Course®).✓ Number of steps✓ SleepData from the activity and sleep monitor will be used✓ Breastfeeding rate (at 1 and 6 months postpartum)

(Based on relevant questionnaire items)✓ Duration of breastfeeding (12 months postpartum)(Based on relevant questionnaire items)✓ Indicators of breastfeeding process, breastfeeding desires (at 1 month postpartum)(Based on relevant questionnaire items)

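### The data-collection list omits the start-of-study attitude and knowledge questionnaire that Table 1 schedules for both groups

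*Protocol article*

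**What the plan says.** The Data collection section of the protocol article lists each questionnaire with its own time points. Where an instrument is given at the start, the list says so: the background form is a start-of-study form, and the depression score is entered as "Edinburgh Postnatal Depression Score (EPDS) (start of study, 1 month postpartum". The attitude and knowledge entry is "Behavioral changes (attitude, knowledge) (6, 12 months postpartum", with no start.

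Table 1, introduced in the same section as the trial's schedule, has a row for "Behavioral changes (attitude, knowledge" with an open circle under the start of trial, 6 months and 12 months. The table's key gives the open circle the meaning of collection in both arms ("Both groups, ● intervention group only").

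Table 2, under Secondary outcomes, marks "Attitude, knowledge" at registration, 6 months and 12 months.

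The Behavioral changes section defines the outcome only as "Based on relevant questionnaire items", with no time points and no change score. Analysis of secondary outcomes plans group means or proportions with 95% confidence intervals, and unadjusted t-tests or chi-square tests between groups.

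**The concern.** The article gives two schedules for one questionnaire, and they differ in whether there is a baseline. The outcome sits under a heading about behavioral change, and the Discussion rests the trial's rationale partly on habits that begin to shift during pregnancy. A measurement at entry is what would let the trial describe such a shift in attitude and knowledge.

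The timing makes the omission hard to repair. The Intervention section starts the intervention on the day of consent and delivers articles on obesity and pregnancy through the application. A start form that was not completed before then cannot be replaced later by an equivalent one. Enrollment had already begun in September 2020 according to Methods/Design, so it matters which schedule was built into the online questionnaires.

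**Working it through.** No figure in the plan needs reproducing. The check sets the schedules side by side, questionnaire by questionnaire.

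| Questionnaire | Data collection list | Table 1 | Agree? |
|---|---|---|---|
| Background, lifestyle | start | start | yes |
| EPDS | start, 1 month | start, 1 month | yes |
| Breastfeeding status | 1, 6, 12 months | 1, 6, 12 months | yes |
| Breastfeeding process | 1 month | 1 month | yes |
| Attitude, knowledge | 6, 12 months | start, 6, 12 months | **no** |
| User-friendliness | 6, 12 months | 6, 12 months | yes |
| Desire to continue | 12 months | 12 months | yes |

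Six of the seven rows match, so the Table 1 columns are being read correctly and the mismatch is not an effect of text extraction. The only difference is the start administration of one questionnaire.

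Table 2 points the same way as Table 1 but is weaker evidence. Its registration column also marks user-friendliness and desire to continue, which neither the list nor Table 1 places at the start.

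Two other statements could fill the gap, and neither does:

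- The general sentence "All participants will complete online questionnaires at the beginning of the study and at 1, 6, and 12 months postpartum" covers the set as a whole. The background form and the EPDS alone satisfy its first time point.
- The background form is described as "items related to pregnancy and delivery history, medical history, family history, and exercise and dietary habits". Attitude and knowledge are not among its contents.

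What each schedule allows for this outcome:

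| Quantity | List followed | Table 1 followed |
|---|---|---|
| Between-group comparison at 6 and 12 months | yes | yes |
| Change from 6 to 12 months | yes | yes |
| Change from study entry | no | yes |
| Adjustment for the start value | no | yes |

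The value of the start form, if it is used, can be sized for a continuous score. Let r be the correlation between the start value and the follow-up value. The documents give no r, so 0.4 to 0.6 is an assumption. The variance of the adjusted group difference, relative to the follow-up-only difference, is 1 − r²:

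- r = 0.4: 1 − 0.16 = 0.84, a 16% reduction. 1/0.84 = 1.19, so the unadjusted comparison would need 19% more women for the same precision.
- r = 0.6: 1 − 0.36 = 0.64, a 36% reduction. 1/0.64 = 1.56, so 56% more women.

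**The case against.** The strongest reply is that a baseline is probably planned. Table 1 is presented as the schedule for the trial, the general sentence about questionnaires at the beginning fits it, and the list entry may simply have dropped a time point. The questionnaires themselves are in a supplementary file that is not shown, so nothing proves that the list is what was implemented. That is fair, and the point is therefore an inconsistency to reconcile; the documents do not show that the baseline was in fact left out.

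It is also fair that the variance gain is not lost through the list alone. The planned tests are unadjusted, so the gain would not be realized under Table 1 either unless the analysis is changed.

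Two stronger readings are tempting, and the documents do not support them:

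- A reader might infer that without the start form no change, or no useful comparison, can be computed. The heading on behavioral change also covers diet, steps, sleep and breastfeeding, and no change score is defined for attitude and knowledge. The planned 6- and 12-month comparison stands under either schedule, and so does a change between those two times.
- A reader might infer that the start score would correct selection arising because each site is told the day's arm before recruitment (Allocation). Adjusting for one score cannot do that in general. The article also says that the recruiting physician is blinded to the allocation (Trial setting, Blinding). How arms are assigned and disclosed is a separate matter.

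**Conclusion.** The contradiction is real and confined to one entry: the list gives 6 and 12 months, while Table 1 gives the start, 6 and 12 months for both groups. If the list governs, change from study entry and baseline adjustment are lost irrecoverably for one secondary outcome. Steps and sleep, under the same heading, have a start measurement in both text and tables. The primary outcome and the sample size are untouched.

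This is a minor point, worth correcting because the correction is cheap and a missed start form cannot be made good. The 16% to 36% variance reduction rests on the assumed correlation, on a continuous score, and on an adjusted analysis that the plan does not yet contain. It measures what could be gained and is not an error in a stated figure.

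**What to change.** - In the Data collection list, change the time points of the attitude and knowledge entry to: start of study, 6, 12 months postpartum. This matches Table 1. State that the start form is completed before the intervention begins.
- In Analysis of secondary outcomes, compare the arms on this outcome at 6 and 12 months adjusted for the start value, in place of the unadjusted t-test.
- State which schedule was actually run. If any women were enrolled without the start form, report them as follow-up only for this outcome.

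The cost is one line in the schedule, one sentence in the analysis section, and one short online form at entry, where other questionnaires are already completed. If Table 1 was the schedule in use, participants carry no added burden.

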### Primary outcome

The primary outcome will be the ratio of change in body weight (%) from pre-pregnancy to 12 months postpartum.

The pre-pregnancy weight will be self-reported, as weights reported by obese individuals have been reported to differ only slightly from actual measurements. The body weight at 12 months postpartum will be directly retrieved from the smartphone application as measured by the device.

### Secondary outcomes

The following items will be evaluated (shown in Table 2):

**Table 2 Tab2:** Primary and secondary outcomes

Outcomes				Trial duration							
					Intervention						Finished
				Registration	During pregnancy	Delivery	1 montha postpartum	6 weeks postpartum	6 months postpartum	12 months postpartum	24 months postpartum
Primary			Rate of change in body weight from before pregnancy to 12 months postpartum	×						×	
Secondary	Health outcomes	Bothgroup	Pregnancy outcomes (cesarean section rate, preterm birth rate, LGA rate, excessively large baby rate, pregnancy-induced hypertension rate, gestational diabetes rate, etc.)			×					
			Rate of change in body weight from before pregnancy	×			×		×		×
			Percentage who reached the weight target						×	×	×
			Body fat ratio				×		×	×	×
			Hypertension rate						×	×	×
			Impaired glucose tolerance rate						×	×	×
			Edinburgh Postnatal Depression Score ≥9 rate	×			×				
	Behavioral changes		Number of steps	×					×	×	×
			Sleep	×					×	×	×
			Attitude, knowledge	×					×	×	
			Breastfeeding rate				×		×	×	
			Breastfeeding process				×				
		Intervention group only	Percentage of carbohydrates, fat, protein, dietary fiber in diet	×					×	×	
	Use of IoT/mobile app		Rate of use of weight-body composition monitor, activity-sleep tracker	×					×	×	
			Number of logins to mobile app, browsing time	×					×	×	
			Meal image/content upload status	×					×	×	
			Intervention program continuation rate						×	×	
			Adherence	×					×	×	×
			Desire to continue using IoT after end of study	×						×	
		Bothgroup	User-friendliness of the devices	×					×	×	

#### Health outcomes

✓ Pregnancy outcomes (gestational age at delivery, cesarean section rate, preterm birth rate, excessively large baby rate, birth height, birth weight, SD value, large-for-gestational-age rate, pregnancy-induced hypertension rate, gestational diabetes rate, etc.)Maternity checkup and pregnancy outcome data will be collected from the Maternal and Child Health Handbook.✓ Weight gain during pregnancy (kg)Calculated as: (weight immediately before delivery retrieved from the Maternal and Child Health Handbook)—(pre-pregnancy weight).✓ Change in weight from before pregnancy to 1, 6, 12, and 24 months postpartum (kg)✓ Rate of change in weight from before pregnancy to 1, 12, and 24 months postpartum (%)

The postpartum weights will be directly retrieved from the smartphone application as measured by the device.✓ Percentage of participants who will reach the target weight (at 6, 12, and 24 months postpartum) (%)A participant will be considered to have reached the postpartum target weight if/when their body weight declines to 93% of the weight before pregnancy.✓ Change in body fat ratio from 1 month postpartum to 6, 12, and 24 months postpartum✓ Percentage of participants with hypertension (excluding those having been diagnosed before pregnancy)The mean of the two blood pressure readings taken at home in the morning and before going to bed will be used. If only one blood pressure reading is taken, that value will be used. Hypertension is defined as a 3-day mean of ≥ 135 mmHg and/or ≥ 85 mmHg.✓ Percentage of participants with impaired glucose tolerance or diabetes (at 6, 12, and 24 months postpartum)Postpartum impaired glucose tolerance is defined as fasting blood glucose ≥ 110 mg/dl and ≤ 125 mg/dl or HbA1c ≥ 6.0% and ≤ 6.4% in the at-home blood samples. Diabetes is defined as a fasting blood glucose level of ≥ 126 mg/dl or HbA1c is ≥ 6.5%.✓ Percentage of participants with EPDS ≥ 9 (start of the study and at 1 month postpartum)

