**Methods:**

Women will be recruited during outpatient maternity checkups at four perinatal care institutions in Japan. We will recruit women at less than 30 weeks of gestation with a pre-pregnancy body mass index ≥ 25 kg/m^2^. The women will be randomly assigned to an intervention or non-intervention group. The intervention will involve using data (weight, body composition, activity, sleep) measured with IoT devices (weight and body composition monitor, activity, and sleep tracker), meal records, and photographs acquired using a mobile application to automatically generate advice, alongside the use of a mobile application to provide articles and videos related to obesity and pregnancy. The primary outcome will be the ratio of change in body weight (%) from pre-pregnancy to 12 months postpartum compared to before pregnancy.

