### Intervention

The intervention will be initiated on the day consent is provided during pregnancy to 1 year postpartum. The IoT intervention for this trial is defined as (1) automatically generated advice based on data (weight, body composition, activity, sleep) measured using IoT devices and meal records and photographs recorded with a mobile application (Calo Mama Plus Pregnant woman Course®) and (2) provision of articles and videos related to obesity and pregnancy via a mobile application.

The following IoT devices will be distributed to all participants: body composition monitor and scale (HBF-227t, Omron Healthcare Inc., Tokyo) and fitness tracker (Fitbit Inspire®, Fitbit Inc., San Francisco, CA).

Participants in the intervention group will use a mobile application (Calo Mama Ninsanpu Plus®). The target weight 1 year postpartum has been set at 93% of the pre-pregnancy weight. Participants will monitor themselves daily to the extent possible using the IoT devices (weight and body composition monitor, activity, and sleep tracker) and by entering meal records and photographs into the mobile application.

The mobile application (Calo Mama Plus Ninsanpu Course®) has the following four functions: 

It automatically generates personalized advice based on conditions during and after pregnancy. Personalized advice is generated automatically based on data (weight, body composition, activity, and sleep) measured with the IoT devices and meal records and photographs recorded by the mobile application, alongside considering how far long in the pregnancy the participant is or the number of weeks postpartum.It provides articles based on the number of weeks of pregnancy or postpartum. The articles are delivered once or twice a week on themes that match the number of weeks of pregnancy or postpartum.It provides breastfeeding advice. After delivery, advice on breastfeeding is provided that reflects the breastfeeding status (number of times the participant recorded breastfeeding and amount of milk).It plots the body weight during pregnancy. Weight measurements during pregnancy are plotted on a graph and advice on weight changes based on the pre-pregnancy BMI is provided.

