### Sample size

Assuming a -2% weight change at 12 months postpartum compared to before pregnancy in the non-intervention group, the trial was designed to detect whether the IoT/mobile application intervention would result in a -5% weight change at 12 months postpartum. To conduct a two-sided test with a standard deviation of 8% and significance level of 5% at 80% power, 226 participants in both groups are needed. Assuming loss of approximately 20% of participants from exclusion or drop-out, the target number of registrations is set to 270 women.

There are 6,000 deliveries each year at the trial institutions. If 10% of the women are obese, the total number comes to 600 per year. As pregnant women at up to 30 weeks of gestation are eligible for registration, 250 pregnant women at up to 30 weeks of gestation who have already visited the outpatient maternity clinic for checkups and 250 pregnant women who newly visit during the 5-month registration period will be eligible. Hence, it is expected to be possible to register the target number of participants.

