### Analysis of secondary outcomes

For continuous variables, the mean and 95% confidence interval will be calculated for each group and t-tests will be used for group comparisons. For discrete variables, the number, proportion, and 95% confidence interval for the proportion will be calculated for each group, and the chi-square test will be used for group comparisons.

Regarding the breastfeeding proportion, ≥ 80% breastfeeding (daily milk amount ≤ 125 ml at 1 month postpartum and ≤ 164 ml at 6 months postpartum) will be used for between-group comparisons. Regarding the dietary items, the means and 95% confidence intervals will be calculated for each item at each time point (at the start of the study and 6 and 12 months postpartum) in the intervention group. The same analysis will be performed to analyze changes from the start of the study to 6 and 12 months postpartum.

For device usage, the use of activity tracker meters, wearing the weight/body composition monitor, and performance of measurements with the weight/body composition monitor at each time point (6 and 12 months postpartum) will be summarized and compared between the groups. In the group that will not use the devices at the beginning of the study, the number, proportion, and 95% confidence interval for the proportion will be calculated for participants who started using the devices at 6 and 12 months postpartum.

Regarding mobile application use, the mean and 95% confidence intervals will be calculated for the number of logins and viewing time at each time point in the intervention group (at 6 and 12 months postpartum). For uploading of meal images (at 6 and 12 months postpartum) and viewing of breastfeeding videos (during pregnancy and at 6 weeks postpartum), the number, proportion, and 95% confidence interval will be calculated for the intervention group.

Regarding the continuation of the intervention program (at 6 and 12 months postpartum), the number, proportion, and 95% confidence interval will be calculated for the intervention group.

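### Gestational diabetes and pregnancy-induced hypertension diagnosed before consent count as trial outcomes, which dilutes two secondary comparisons

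*Protocol article*

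**What the plan says.** - **Outcome.** The Health outcomes section lists the pregnancy outcomes, among them "large-for-gestational-age rate, pregnancy-induced hypertension rate, gestational diabetes rate". On the source it says: "Maternity checkup and pregnancy outcome data will be collected from the Maternal and Child Health Handbook". Table 2 places these outcomes at delivery, for both groups.
- **Entry.** The Abstract states: "We will recruit women at less than 30 weeks of gestation". The Participants section sets the same limit at consent. Its only glucose-related exclusions are diabetes known before pregnancy and overt diabetes found during it. Neither existing gestational diabetes nor existing pregnancy-induced hypertension is named. The one remaining filter is the physician's general judgement that a woman is unsuitable.
- **Start of exposure.** The Intervention section says: "The intervention will be initiated on the day consent is provided during pregnancy to 1 year postpartum".
- **Analysis.** For discrete secondary outcomes, "the chi-square test will be used for group comparisons". No adjustment for status at entry is described.
- **Recruitment pool.** The Sample size section expects "250 pregnant women at up to 30 weeks of gestation who have already visited the outpatient maternity clinic for checkups", plus 250 women who newly visit during registration.

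**The concern.** Most items in the list of pregnancy outcomes, such as cesarean section, preterm birth and birth weight, are fixed at delivery and so always follow consent. Gestational diabetes and pregnancy-induced hypertension differ, because either may be diagnosed before a woman who enters late in the window gives consent. The article treats all items alike, as undated rates for the pregnancy.

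A case that precedes consent adds equally to both arms on average and cannot respond to the intervention. The risk ratio then mixes a part that can move with a part that cannot. At stake is the reading of two secondary comparisons: a real reduction in new cases would look smaller than it is and would be harder to detect, and a chance difference in prior cases could be taken for an effect or hide one.

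**Working it through.** **The plan's own figure.** There is none for these two outcomes. The stated total of 226 concerns weight at 12 months; it reproduces (difference 3 points, SD 8%: 224 by the normal approximation, 226 by the t-test version) and has no bearing here.

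**Step 1: does the text let a prior case count?** Set the sections side by side. Entry is open until 30 weeks (Participants). Exposure begins at consent (Intervention). Women already diagnosed with either condition are not excluded (Participants). The outcome is an undated rate read from the Handbook (Health outcomes) and compared without adjustment (Analysis of secondary outcomes). Nothing removes a prior case from the numerator or the denominator. That the rate covers the whole pregnancy is an inference, but it is the plain reading.

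**Step 2: illustration of size.** Every rate below is an assumption.

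Inputs: share already diagnosed at consent *q* = 10%; later incidence among the rest *c* = 15% in controls and *t* = 7.5% with the intervention (true risk ratio 0.50); 135 per arm, which is the registration target of 270 divided by 2, assuming equal arms and no loss.

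Observed rate = *q* + (1 − *q*) × later incidence:
- control: 0.10 + 0.90 × 0.15 = 0.235
- intervention: 0.10 + 0.90 × 0.075 = 0.1675
- observed risk ratio: 0.1675 / 0.235 = 0.71

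Power (arcsine approximation, two-sided 5%) = Φ(h√(n/2) − 1.96), with h = 2·arcsin√p₁ − 2·arcsin√p₂:
- as written, n = 135: h = 0.169, h√(n/2) = 1.388, power 28%
- new cases only, n = 135 × 0.90 = 121.5: h = 0.241, h√(n/2) = 1.875, power 47%

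**Step 3: vary the assumptions** (later incidence in controls 15%, 135 per arm).

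| Prior cases | True RR | Observed RR | Power as written | Power, new cases only |
|---|---|---|---|---|
| 5% | 0.50 | 0.63 | 37% | 49% |
| 10% | 0.50 | 0.71 | 28% | 47% |
| 15% | 0.50 | 0.77 | 23% | 45% |
| 10% | 0.70 | 0.83 | 12.5% | 18.3% |
| 10% | 0.80 | 0.89 | 7.7% | 10.1% |

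A second set of assumptions agrees in direction. Take 113 per arm, a whole-pregnancy control rate of 20%, half of the cases before consent and a true risk ratio of 0.60 on later cases. The observed ratio is (0.10 + 0.10 × 0.60) / 0.20 = 0.80, and power is 12% as written against 20% for new cases only. With control rates of 10% and 30%, the pairs are 8% against 12% and 17% against 29%.

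**Step 4: chance imbalance.** With 10% prior cases and 135 per arm, the difference in prior share between arms has a standard deviation of √(2 × 0.10 × 0.90 / 135) = 3.7 percentage points. The intervention's contribution in Step 2 is 23.5 − 16.75 = 6.75 points. This noise is already part of the lower power as written.

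**The case against.** **The text is silent rather than wrong.** The items stand in a bracketed list that ends open, none with a counting window, and a condensed article may leave such detail to the full protocol. The baseline questionnaire covers pregnancy and medical history, so status at entry may already be captured. This lowers the severity. It does not remove the point: the outcome as stated gives a diluted contrast, and a better definition is easy to state.

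**The size is assumed.** This stands. No rate for either condition is given, one set of shares is used for both, and a true ratio of 0.50 is favourable. At 0.70 or 0.80, both definitions have little power.

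**The whole-cohort risk difference is not biased when the arms are comparable.** This also stands. In the illustration it is 6.75 points over all women against 7.5 among those at risk. What is diluted is the risk ratio, and with it power.

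Three stronger readings are tempting and not supported:
- A reader might infer that the plan contradicts itself, because for the postpartum outcome it specifies "Percentage of participants with hypertension (excluding those having been diagnosed before pregnancy". That clause removes disease known before pregnancy, not disease diagnosed before consent. The entry criteria do the same for diabetes. Prior diagnoses within the pregnancy are removed in neither place, so there is no inconsistency.
- A reader might infer that a diagnosis makes staff readier to offer the app, so that prior cases pile up in one arm. Sites are told the allocation before each day's recruitment, but that is a separate issue touching every outcome. The recruiting physician is stated to be blinded (Trial setting, Blinding). The documents do not show unequal selection by diagnosis.
- A reader might take the 250 women already attending, half of the expected 500, as a measure of prior cases. The article gives neither their gestational ages nor their diagnoses, so the figure shows only that late entry is possible.

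**Conclusion.** The point holds in a limited form. As written, gestational diabetes and pregnancy-induced hypertension diagnosed before consent count as outcome events. With comparable arms the consequence is a risk ratio pulled towards 1, lower power and added noise; bias in favour of one arm is not shown.

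The number of prior cases, and hence the size, cannot be determined from the article. The shift from 0.50 to 0.71, with power of 28% instead of 47%, rests wholly on the assumed 10% prior cases, 15% versus 7.5% later incidence and 135 per arm. The primary outcome is untouched, and the trial was not sized for either of these outcomes. Severity is minor: a cheap improvement. If the full protocol already limits the window to diagnoses after consent, the article's wording only needs to be aligned with it.

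**What to change.** For the between-group comparison, define each of the two outcomes as a first diagnosis after the date of consent, among women without that diagnosis at consent. Apply this to each condition separately, so that a woman with one prior diagnosis still counts for the other. Report the number already diagnosed at consent by arm as a baseline characteristic. Keep the rate over the whole pregnancy as a descriptive figure without a test.

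Cost: a change of wording and a smaller denominator (121.5 instead of 135 per arm in the illustration). Status at consent or the diagnosis date must be taken from the Handbook or the medical record. The article does not say that the retrieved data carry diagnosis dates, so this should be confirmed before the definition is fixed.
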